### Exploratory outcomes

Exploratory outcomes comprise rates of GP consultation and medication changes, diagnostic metrics of multiparametric testing and individual test categories. Diagnostic metrics are assessed including sensitivity, specificity, positive predictive value (PPV), and negative predictive value (NPV). To further assess feasibility from participant perspective, the theoretical framework of acceptability (TFA Questionnaire) is used with the outcome of a median Likert-scale score of ≥ 4 for each item [21].

In addition, pharmacy-level data will be collected to describe heterogeneity across implementation sites and to support interpretation of pharmacy-level differences in feasibility and screening yield. These data will be separated into baseline pharmacy characteristics, implementation process metrics and recruitment process evaluation (Supplementary Table 2). Baseline pharmacy characteristics include staff size, number of pharmacists, pharmacy setting, approximate number of customers per day, opening hours, Saturday opening, status as the only pharmacy in town, prior experience with point-of-care testing or other structured pharmaceutical services, availability of a dedicated consultation area, availability of customer restroom facilities, stable internet access in the testing area, and existing collaboration with local general practitioners.

Pharmacy-level implementation process metrics will include the number of recruited participants per pharmacy, recruitment rate, recruitment pathway, sex and age distribution of recruited participants, inclusion criteria distribution, estimated time required per screening, staff group conducting the screening, technical issues, staff shortages during the recruitment period, perceived documentation burden, workflow compatibility, and main barriers to recruitment and screening completion. Furthermore, a recruitment process evaluation will assess factors influencing patient recruitment. These variables will be analyzed descriptively to explore heterogeneity across participating pharmacies and to inform the design of future larger-scale studies.

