### Study setting and pharmacy selection

The study takes place in the outpatient setting with a planned number of 20 participating pharmacies. This number was chosen pragmatically for the pilot implementation phase to balance sufficient recruitment capacity with feasibility of onboarding, monitoring, technical support, and confirmatory follow-up. Each pharmacy is expected to recruit approximately 50 participants, resulting in a total planned sample size of 1,000 participants.

Pharmacies will be selected in collaboration with the Pharmacists’ Association of Schleswig-Holstein. The Association invited community pharmacies in Schleswig-Holstein to express interest in participation. From this pool of interested pharmacies, sites will be selected purposively according to predefined implementation-relevant criteria. First, we aim to include 10 pharmacies located in the region of the study center and 10 pharmacies located at greater distance from the study center. Second, within each of these two groups, we aim to include five pharmacies with customer restroom facilities allowing on-site urine albumin-creatinine ratio (UACR) testing and five pharmacies without such facilities, resulting in 10 pharmacies with and 10 pharmacies without on-site UACR testing capacity. Third, pharmacies will be selected to ensure broad geographic coverage across Schleswig-Holstein, including northern, southern, western, and eastern regions of the federal state.

This selection strategy is not based on random sampling and is not intended to generate a representative sample of all German community pharmacies. Rather, it is a purposive implementation-oriented sampling strategy designed to capture relevant heterogeneity in pharmacy infrastructure, distance to the study center, and regional accessibility within Schleswig-Holstein.

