### Primary outcomes

The study will assess three primary outcomes:

(I)Participant-level feasibility is assessed by screening completion rates of participants who provided informed consent. The outcome is defined as completion of the structured questionnaire, performance of blood pressure measurement and PoC-testing for dyslipidemia and HbA1c. The study aims for an overall completion rate ≥ 70% based on the reported use of primary care screenings and prospective feasibility on the national level in Germany.(II)Implementation outcomes from the pharmacy perspective are evaluated for the implementation domains acceptability, feasibility, and sustainability. The outcome is evaluated using validated instruments, including the Acceptability of Intervention Measure (AIM), the Feasibility of Intervention Measure (FIM), and the Normalization Measure Development Questionnaire (NoMad) to assess sustainability (Supplementary Tables 1 and NoMad Questionnaire) [16–19]. These instruments use standardized self-administered questionnaires completed by pharmacy staff that are rated on Likert scales. Validated German versions will be used. For each domain, the outcome criterion is defined by a null hypothesis assuming a median Likert-scale score ≤ 3. Rejection of the null hypothesis will be interpreted as evidence of sufficient implementation performance under routine practice conditions.(III)The medical screening yield is quantified by the number needed to screen (NNS) to identify at least one previously unknown or insufficiently managed CKM syndrome risk factor. These are defined as non-HDL cholesterol ≥ 5.7 mmol/L for known dyslipidemia or lipid-lowering therapy, HbA1c ≥ 8.5% in participants with known diabetes mellitus, positive albuminuria test without RASi or SGLT2i therapy in participants with CKD, or blood pressure ≥ 140/80 mmHg for participants with known hypertension. A NNS ≤ 5 will be considered as indicative of a clinically meaningful detection efficiency of the multi-parametric screening approach. Further, a NNS between 5 and 10 will be considered an exploratory finding indicating the need for potential refinement or modification of the screening strategy. An observed NNS > 10 will be interpreted as an unfavorable feasibility outcome under routine practice conditions.

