An NNS of ≤ 5 was predefined as a pragmatic threshold for clinically meaningful detection efficiency. This threshold reflects the identification of one previously unknown or insufficiently managed actionable risk factor in 20% of screened at-risk individuals. Although this is not directly comparable to outcome-based NNS estimates from established screening programs, it is expected to correspond to a downstream NNS to prevent one clinical event of approximately 100–150, assuming that detected abnormalities trigger evidence-based treatment with numbers needed to treat of around 20–30. Against this background, and considering that accepted screening programs often operate with substantially higher outcome-based NNS values, an NNS ≤ 5 was considered a clinically relevant benchmark for this pilot study [20].

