### Sample size and statistical analysis

The planned sample size of 1000 participants allows for reliable estimation of key outcomes with 95% confidence intervals with an estimation error of approximately ± 5%. With an expected prevalence of 50% of risk factors and 10 pharmacies in the region of the study center, we expect 250 participants with indication for confirmatory testing at the study center. At an expected attrition of 20%, 200 participants should complete confirmatory testing. This allows for determination of false-positive rates and test specificity with acceptable precision (± 10%). Attrition in the GP-confirmatory testing arm is expected to be higher, but will be minimized through repeated digital or telephone prompts and, if necessary, invitation for testing at the study center. Statistical analysis will be descriptive, using frequency tables, means (± standard deviation), medians (± interquartile range) for Likert-Scale analysis, and proportions with 95% confidence intervals. Diagnostic metrics (sensitivity, specificity, PPV, NPV) will be determined. Sensitivity of the PoC test can be assessed based on the results from the confirmatory testing. Scale scores for implementation metrics will be calculated as the mean of the respective items, with higher values indicating greater agreement and lower values indicating greater disagreement.

Feasibility and clinical outcomes will be summarized overall and, where appropriate, descriptively at pharmacy level. Pharmacy-level summaries will include recruitment numbers, screening completion rates, confirmatory testing uptake, diagnostic yield, and implementation scores. Baseline pharmacy characteristics will be used to contextualize variation across pharmacies, whereas pharmacy-level implementation process metrics will be interpreted as outcomes of the implementation process. Given the limited number of participating pharmacies, these analyses will be exploratory and hypothesis-generating. Confirmatory inference regarding pharmacy-level predictors is not planned.

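### Pharmacy-level completion and yield are only to be described, on about 50 participants per site; the raw spread overstates heterogeneity, and an estimated between-pharmacy variance should stand beside it

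*Protocol article*

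**What the plan says.** Two sections of the Protocol article have to be read together.

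- **Exploratory outcomes** gives the purpose. Pharmacy-level data are collected to describe how sites differ and to help interpret site differences in feasibility and yield. The section then lists baseline characteristics, process metrics and a recruitment evaluation, and closes: "These variables will be analyzed descriptively to explore heterogeneity across participating pharmacies and to inform the design of future larger-scale studies".
- **Sample size and statistical analysis** gives the method for the site rates themselves: "Pharmacy-level summaries will include recruitment numbers, screening completion rates, confirmatory testing uptake, diagnostic yield, and implementation scores". These summaries are descriptive, and baseline characteristics are used to put the variation in context. The section calls the site analyses exploratory because there are few pharmacies, and rules out confirmatory inference on pharmacy-level predictors. It plans confidence intervals for proportions without saying whether that applies site by site. It names no ICC, between-pharmacy variance, random-effects model or shrinkage.

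The site numbers come from **Study setting and pharmacy selection**: a "planned number of 20 participating pharmacies", and "Each pharmacy is expected to recruit approximately 50 participants, resulting in a total planned sample size of 1,000 participants".

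**The concern.** The observed spread of site rates has two parts: real differences between pharmacies, and binomial chance from having about 50 people at each. A descriptive table shows the sum and cannot split it. The stated purposes, describing heterogeneity and informing a larger study, need the first part alone.

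Two things are at stake. Pharmacy features such as staffing or premises could be offered as the background to differences that are mostly noise. And if the spread of raw rates is carried into the planning of a larger study, it is too large a figure for between-pharmacy variation. The point is about reading differences between sites, not about the width of the overall confidence intervals.

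**Working it through.** **Inputs from the documents.** 20 pharmacies and about 50 participants each (Study setting and pharmacy selection). Completion of 70%, from "The study aims for an overall completion rate ≥ 70" per cent (Primary outcomes). Yield of 20%, from the NNS benchmark of 5, explained there as "identification of one previously unknown or insufficiently managed actionable risk factor in 20% of screened at-risk individuals".

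**Assumptions.** The 70% and 20% are the plan's benchmarks, used here as common true rates; they are not the plan's forecasts. Site sizes are taken as equal. The ICC values are assumed, since the document gives none.

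**Step 1: the plan's own figure.** 20 × 50 = 1,000, which reproduces. The overall precision, "reliable estimation of key outcomes with 95% confidence intervals with an estimation error of approximately ± 5" per cent, is not in dispute: simple binomial precision at n = 1,000 and p = 0.5 is 1.96 × √(0.25/1,000) = ±3.1 points, inside the stated margin. That statement concerns overall outcomes and says nothing about single sites.

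**Step 2: chance spread with identical sites.** SD of a site rate = √(p(1−p)/n); 95% half-width = 1.96 × SD. The lowest and highest values are means over 200,000 simulated sets of 20 binomial sites.

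| Outcome | p | n per site | SD (points) | 95% half-width (points) | Mean lowest – highest | Mean range (points) |
|---|---|---|---|---|---|---|
| Completion | 0.70 | 50 | √(0.21/50) = 6.5 | 12.7 | 58% – 82% | 24 |
| Yield | 0.20 | 50 | √(0.16/50) = 5.7 | 11.1 | 10% – 31% | 21 |
| Yield, completers only | 0.20 | 35 (0.70 × 50) | √(0.16/35) = 6.8 | 13.3 | 8% – 33% | 25 |

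The third row matters because the NNS denominator is restricted to participants with completed screening (Missing data).

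**Step 3: how much of the observed variance is chance.** With an intraclass correlation ICC:

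- true SD = √(p(1−p) × ICC)
- observed SD = √(p(1−p) × (ICC + (1−ICC)/n))
- chance share = ((1−ICC)/n) / (ICC + (1−ICC)/n), which does not depend on p

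At p = 0.70, n = 50 and ICC = 0.01: true SD = √(0.21 × 0.01) = 4.6 points; observed SD = √(0.21 × (0.01 + 0.0198)) = √(0.21 × 0.0298) = 7.9 points; chance share = 0.0198/0.0298 = 66%. The chance share at other values is in the table under Step 4.

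**Step 4: what 20 sites of 50 can deliver.** The last column is the 95% sampling range of the ANOVA estimate of the ICC (p = 0.70, 40,000 simulations).

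| True ICC (assumed) | Chance share of observed variance | Sampling range of estimated ICC |
|---|---|---|
| 0.01 | 66% | −0.006 to 0.032 |
| 0.02 | 49.5% | −0.001 to 0.049 |
| 0.05 | 28% | 0.014 to 0.097 |
| 0.10 | 15% | 0.040 to 0.177 |

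The raw spread is biased upward at every value, most where true differences are small. The ICC estimate is imprecise but removes that bias.

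**The case against.** The strongest reply is that the plan is already cautious. It calls the site analyses exploratory and hypothesis-generating, excludes confirmatory inference on predictors, and plans intervals for proportions. If given per site, intervals of about ±12.7 points would display the noise. This stands, and it lowers the weight of the point. It does not remove it: twenty wide intervals still do not estimate the variance between sites, and an exploratory label does not separate signal from chance.

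Three stronger readings are tempting, and the documents do not support them.

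- *Chance will be reported as site differences, with sites ranked as good or poor.* Nothing in the text says so. The 70% target is for the overall completion rate, and the NNS bands judge the screening approach as a whole; no site is to be passed or failed. Counting how many sites miss 70%, or show an NNS above 10, describes a judgement that is not planned. Such counts also depend heavily on the assumed rate: at a 20% yield the chance that at least one of 20 identical sites exceeds an NNS of 10 is 71% with 35 completers per site and 31% with 50, and at a 30% yield with 35 completers it is about 5%. The plan's only stated expectation, "With an expected prevalence of 50% of risk factors and 10 pharmacies in the region of the study center", uses 50%. That figure concerns the indication for confirmatory testing, not the NNS event, but at that rate the chance is practically nil.
- *The next study gets no usable variance figure.* For a binary outcome an ICC can be calculated later from site counts and denominators, and Data Availability provides for sharing individual data. What is absent is a planned figure.
- *The closing sentence of Exploratory outcomes itself fixes how completion and yield are read.* That sentence refers to site characteristics, process metrics and the recruitment evaluation, many of which carry no binomial error. The site rates are governed by Sample size and statistical analysis, so the point belongs there.

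It is also fair to say that a fuller plan, not shown, may name a variance estimate, and that a descriptive analysis does not exclude one.

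**Conclusion.** The point holds at modest weight. The article states a purpose, describing heterogeneity and informing larger studies, and a method, descriptive site summaries, that serves it only in part. With about 50 participants per site and no true differences, chance alone gives a spread of about 24 points in completion (at 70%) and 21 points in yield (at 20%). At an assumed ICC of 0.01 the observed SD of site completion would be 7.9 points against a true 4.6; at 0.10 chance falls to 15% of the variance, so the size of the overstatement depends on an ICC that nobody yet knows.

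The raw spread may therefore be misread, though the plan does not commit to misreading it. No primary estimate, threshold or decision rule is affected. The conclusion rests on the common rates of 70% and 20%, on equal site sizes and on the assumed ICC range.

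**What to change.** In Sample size and statistical analysis, for screening completion and for the unadjusted yield:

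1. Fit a random-intercept logistic model with pharmacy as the random effect. Report the between-pharmacy SD or ICC with a 95% CI beside the site rates.
2. Plot the site rates against funnel limits around the overall rate, with each site's own denominator.
3. State that spread inside those limits is not by itself evidence of heterogeneity. With 95% limits, about 20 × 0.05 = 1 site is expected outside by chance, so one site outside should not be over-read either.

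The cost is two models and one plot from data already collected, with no change to any primary outcome. The drawback is precision and reach: the estimated ICC would vary between about −0.006 and 0.032 at a true 0.01, and between 0.014 and 0.097 at a true 0.05. Because the pharmacies are selected purposively, it describes these 20 sites rather than pharmacies in general. The report should say both. This is an optional improvement, not a condition for the trial.

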### Inclusion and exclusion criteria

Eligible participants are adults aged 40 years or older who visit a participating pharmacy and meet at least one of the criteria summarized in Table 1. Recruitment of the pharmacies will be done sequentially over a 3-month period, starting from 1 April 2026. Each pharmacy will have 6 months to enroll 50 customers in the study.

**Table 1 Tab1:** Inclusion and exclusion criteria

Inclusion criteria	Exclusion criteria
Age ≥ 40 **and**	Participation in another study
Established regular GP **and**	Inability to give informed consent
Active smoking **or**	
Prescription of antihypertensive, antidiabetic, or lipid-lowering medication **or**	
Obesity (BMI ≥ 30 kg/m²; waist circumference ≥ 88 cm for women or ≥ 102 cm for men)	

### Procedures, data source and collection

#### Participant selection

Pharmacy customers will either be approached during a regular visit or contacted in advance, if they have authorized their pharmacy to inform them of health improvement projects. Potential participants based on the identification of risk medications will be identified via the pharmacy’s dispensing software. These medications will be pre-labeled within the internal inventory system, prompting a targeted invitation to the screening. A list of the drugs that are considered for the inclusion criteria is provided in Supplementary Table 3. Additionally, individuals may proactively ask for inclusion if they self-report to be active smokers, have a body mass index (BMI) ≥ 30 kg/m², or increased waist circumference (≥ 88 cm for women and ≥ 102 cm for men). Participating pharmacies will be instructed to aim for an approximately equal distribution of male and female participants.

The primary aim of this pilot implementation study is not to generate a population-representative prevalence estimate, but to evaluate whether a low-threshold CKM screening pathway can be implemented in community pharmacies with acceptable workflow burden. Therefore, pharmacies are allowed flexibility in recruitment as long as participants meet predefined eligibility criteria. This design is intended to preserve feasibility and external validity under routine pharmacy conditions. More restrictive recruitment procedures, such as strict consecutive sampling or quota-based recruitment, may reduce selection bias but would also increase workload and could impair recruitment, completion rates, and pharmacy engagement. To address selection bias, study monitoring will be implemented to improve balanced recruitment. Participating pharmacies will receive feedback after the inclusion of 25 participants. In addition, feedback will be provided if a male-to-female ratio of 3:1 is reached.

#### Implementation

An encompassing on-boarding concept will be applied to optimize implementation of the multi-parametric screening in pharmacies. This will include on-site training on the general project workflow, the use of the PoC tests and correct documentation. Training will be provided by the study team and PoC-device distributor Medic-SH. Informational videos and hand-outs demonstrating the correct application of the PoC tests will be made available to the pharmacies and participants. Technical support provided by the study center will be available to pharmacists and participants throughout the entire duration of the study. The screening is conceptually based on established and reimbursed clinical pharmacy services. Within APOSCREEN-1, community pharmacies receive a reimbursement of €50 per completed screening [22].

### Data source and collection at screening

In the initial visit, written informed consent will be obtained by the pharmacist and relevant data will be documented using an electronic case report form (eCRF). Table 2 displays the data collected at different time points. Subsequently, participants undergo standardized PoC assessments including albuminuria, blood pressure, HbA1c and full lipid profile (total cholesterol, non-high-density lipoprotein (non-HDL-C) cholesterol, HDL cholesterol (HDL-C), low-density lipoprotein cholesterol (LDL-C) and triglycerides). In pharmacies equipped for on-site PoC testing of albuminuria and blood pressure, all tests will be conducted at the initial visit. Alternatively, patients will be provided with validated home blood pressure monitors and semi-quantitative albuminuria tests along with instructions for testing. Results will be assessed in a second appointment in the pharmacy, together with PoC testing for HbA1c and lipid profile.

**Table 2 Tab2:** Data collected within the eCRF

Category	Data collected		
	At Screening	At Confirmatory Testing	At Follow-Up
Demographic data	• age • gender • postal code • educational level • employment status • type of health insurance		
History	• currently prescribed medication list • pre-existing medical conditions • family history of cardiovascular disease • smoking status • last participation in a health check-up		• medication • visits to the general practitioner after screening findings and therapy • changes from the GP visit • satisfaction with screening / self-assessed benefit of the project
Clinical	• home blood pressure (3x) • body weight • body height • calculated BMI • waist circumference	• 24-hour blood pressure	
Laboratory	• HbA1c • lipid profile (total cholesterol, non-HDL-cholesterol, calculated LDL, HDL, triglycerides) • albuminuria (albuminuria test or urine-albumin-creatinine-ratio)	• HbA1c • fasting plasma glucose • lipid profile (total cholesterol, LDL, HDL, triglycerides, lipoprotein(a)) • creatinine, cystatin c • urine-albumin-creatinine-ratio	

GP, General Practitioner; HDL, high-density lipoprotein; LDL, low-density lipoprotein, BMI, body mass index

